### Statistical analysis

Descriptive analysis of presenting syndromes, fever aetiologies, clinical outcomes as well as candidate predictors (baseline clinical and biochemical parameters) will be carried out. Reasons for important discrepancies will be explored across sites and the derivation dataset for the prediction model will be defined. This derivation dataset will contain the outcomes (table 3), baseline clinical data and host biomarkers (table 1) to be included in the prediction model. Preliminary covariate selection has already been informed by subject knowledge using systematic literature review and expert judgement.^31 32 37^

Penalised ordinal logistic regression (or its multinomial equivalent if assumptions about proportionality between outcome categories are not met) will be used for further covariate selection in order to determine the final model. For continuous variables, transformations will be used if necessary. If feasible, bootstrapping will be used to estimate model performance (discrimination and calibration) and estimate the amount of optimism in the derivation dataset.

The final model obtained from the derivation dataset will be applied on the validation dataset and its performance will be evaluated. The c-statistic will be used to examine discrimination and calibration plots for calibration. The performance of the model at different predicted probability thresholds will be examined.

A full case analysis will be conducted if the overall amount of missing data is less than 5%. If the fraction of missing data is more than 5% then multiple imputation will be used and regression estimates will be combined using Rubin’s rule. Imputation will be conducted separately for the derivation and validation datasets.

The performance of the prediction model derived in the primary analysis will be examined in children presenting with specific clinical syndromes (eg, acute respiratory infections, diarrhoeal disease or acute undifferentiated fever) and fever aetiologies. Performance will be reported using classification tables (confusion matrices) of observed probabilities against predicted probabilities.

Additional protocol-specified secondary analyses will be conducted using alternative approaches for outcome classification (eg, binary and continuous) to explore the impact on the development of the prediction model (see the Discussion section).

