**Methods and analysis:**

This prospective observational study will recruit at least 4900 paediatric inpatients and outpatients under the age of 5 years presenting with an acute febrile illness to seven hospitals in six countries across Asia. A venous blood sample and nasopharyngeal swab is collected from each participant and detailed clinical data recorded at presentation, and each day for the first 48 hours of admission for inpatients. Multianalyte assays are performed at reference laboratories to measure a panel of host biomarkers, as well as targeted aetiological investigations for common bacterial and viral pathogens. Clinical outcome is ascertained on day 2 and day 28.

Presenting syndromes, clinical outcomes and aetiology of acute febrile illness will be described and compared across sites. Following the latest guidance in prediction model building, a prognostic clinical prediction model, combining simple clinical features and measurements of host biomarkers, will be derived and geographically externally validated. The performance of the model will be evaluated in specific presenting clinical syndromes and fever aetiologies.

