### Participant follow-up and outcome measurement

All children are followed up by the research team on day 2 (window period:+2 days) and day 28 (window period +7 days). Follow-up is conducted face to face (via return to the study site or community outreach visit) or via telephone, depending on the constraints at the different study sites. The clinical outcome of the acute febrile illness is recorded, including the details of any further care sought between enrolment and the follow-up contact. In the event that a participant is uncontactable, a minimum of two further contacts are attempted during the window period before a participant is declared lost to follow-up. In addition, admitted children are followed up each day for the first 2 days of their admission and on the day of discharge. Information on the treatment administered by the clinical team, as well as discharge diagnosis, are extracted from the participant’s medical record. A full schedule of enrolment and assessments is provided in the online supplemental file (S1).

Outcome categories are ordinal (1–4) and calculated on day 28 (window period:+7 days) using a composite of vital status, receipt or referral for organ support (defined as mechanical or non-invasive ventilation, receipt of inotropic therapy or renal replacement therapy), length of inpatient hospital stay (at the study site or other health facility) and persistence of symptoms present at enrolment (table 3).

**Table 3 T3:** Outcome categories

Outcome Category	Definition
1	Death or receipt of organ support* ≤48 hours after enrolment
2	Death >48 hours after enrolment and before D28 AND did not meet criteria for severe disease *or* Admitted for >48 hours at any health facility before D28 AND did not meet criteria for severe disease
3	Admitted for ≤48 hours at any health facility before D28 AND did not meet criteria for severe or probable severe disease *or* Not admitted to any health facility AND ongoing symptoms at D28
4	Not admitted to any health facility AND symptoms resolve by D28

*Organ support defined as receipt of or referral for mechanical or non-invasive ventilation, inotropic support or renal replacement therapy.

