### Sample size considerations

By using a conservative estimate of R^2^, a shrinkage factor of 0.9 and a prevalence of severe outcomes (outcome category 1) of 13%,^33 34^ we estimated that we would need approximately 14 events per parameter for derivation of the prediction model.^35^ The derivation dataset will consist of at least 3600 children, with oversampling of those more likely to develop a severe outcome (2400 admitted children and 1200 children whom the treating clinician decides to send home without admission). Based on our estimated prevalence, we would expect to recruit 280 children who progress to meet the primary endpoint (outcome category 1), permitting evaluation of up to 20 candidate predictors, while minimising the risk of overfitting and allowing for up to a 10% attrition rate. This sample size is the minimum number of children that we aim to recruit. If feasible, we will allow for the possibility of recruiting a higher number of participants, as this will permit inclusion of more candidate predictors in the model.

The validation dataset will be geographically distinct and will consist of at least 1000 admitted children and 300 children sent home without admission, providing a total (enriched) sample of 1300 children. Based on the same estimated prevalence and attrition rate, this would provide us with at least the required 100 outcome events in the validation dataset.^36^

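### The subgroup performance table is mis-specified: it names a confusion matrix but describes observed against predicted probabilities, and it is the only measure named for syndromes and aetiologies

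*Protocol article*

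**What the plan says.** The abstract makes subgroup performance a deliverable: "The performance of the model will be evaluated in specific presenting clinical syndromes and fever aetiologies". In the Statistical analysis section, the paragraph on syndromes and aetiologies gives one reporting rule: "Performance will be reported using classification tables (confusion matrices) of observed probabilities against predicted probabilities".

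Three other statements bear on it.

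- Participant follow-up and outcome measurement: "Outcome categories are ordinal (1–4) and calculated on day 28". Table 3 places each child in one of the four categories.
- Statistical analysis, model: a penalised ordinal logistic regression, or a multinomial one if proportionality fails. Either gives four predicted probabilities per child.
- Statistical analysis, validation paragraph: "The c-statistic will be used to examine discrimination and calibration plots for calibration", followed by "The performance of the model at different predicted probability thresholds will be examined". Both sentences concern the final model applied to the validation dataset. The subgroup paragraph comes later and does not repeat them.

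**The concern.** A confusion matrix crosses the observed class with the predicted class. The observed side here is a category from 1 to 4, and an individual child has no observed probability. Observed proportions can be set against predicted risk for groups of children, but that is a calibration table. Two analysts following the sentence could therefore produce different outputs, one a classification table and the other a calibration table.

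The choice matters because the subgroup paragraph names no other measure. If the table is built as a confusion matrix, probabilities must first be turned into classes. Category 1 is uncommon, so the usual default rules seldom predict it even when the model ranks children well. A reader comparing syndromes could then take a difference in event frequency for a difference in model performance.

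**Working it through.** **1. Category 1 frequency in the enriched sample.** Inputs from Sample size considerations: 13% prevalence of category 1, 10% attrition, and a derivation set of "2400 admitted children and 1200 children whom the treating clinician decides to send home without admission".

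- Events: 2400 × 0.13 × 0.90 = 280.8, which reproduces the stated 280. It also agrees with 20 predictors × 14 events = 280.
- Applying 13% to all 3600 children gives 421.2, which does not reproduce it. The 13% therefore acts as a rate among admitted children.
- Frequency after attrition: 280.8 / (3600 × 0.90) = 280.8 / 3240 = 8.7%.
- Validation set: 1000 × 0.13 × 0.90 = 117 events in 1300 × 0.90 = 1170 children, or 10.0%.

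**2. Most-probable-category rule.** The article gives neither an expected c-statistic nor the split of categories 2 to 4, so both are assumed. The simulation uses a correctly specified proportional-odds model with a normal linear predictor (SD 1, 1.5 or 2) and thresholds solved to give the category proportions. Each child is assigned to the category with the highest predicted probability. The table shows the share of category 1 children labelled category 1.

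| c for category 1 | Split 8.7/38/23/30 | Split 8.7/25/33/33 |
|---|---|---|
| 0.75 | 3% | 5% |
| 0.83 | 15% | 18% |
| 0.88 to 0.89 | 28% | 31% |

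A wider set of four splits gives 10–19% at c about 0.80, 23–37% at about 0.87, 37–52% at about 0.91 and 54–62% at about 0.95.

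**3. Where the others are placed.** With 8.7/30/28/33.3 and c = 0.866, category 1 children are labelled 1, 2, 3 and 4 in 24%, 64%, 9% and 3% of cases. Most of those not labelled 1 fall in category 2 in the three splits with 25–40% of children in category 2. With only 10% in category 2 (8.7/10/48/33.3), the figures at the same c are 37%, 0%, 61% and 2%, so they fall in category 3.

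**4. A 0.5 cut-off on category 1 risk.** Equal-variance binormal model, perfectly calibrated, prevalence π and cut-off t:

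- d = √2 · z(c)
- x = [logit(t) − logit(π) + d²/2] / d
- sensitivity = 1 − Φ(x − d)

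For c = 0.85, π = 0.0867, t = 0.5: d = 1.466; x = (0 + 2.355 + 1.074) / 1.466 = 2.340; sensitivity = 1 − Φ(0.874) = 19%. At c = 0.80, 0.90 and 0.95 the same formula gives 8%, 35% and 56%. If weighting brought prevalence down to an assumed 2%, sensitivity would be 11% at c = 0.90 and 30% at c = 0.95.

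**5. Comparison between subgroups.** With predictor strength fixed (SD 1.5) and only the category 1 frequency raised from 3% to 20%, the c-statistic moves from 0.84 to 0.82. The share found by the most-probable-category rule moves from 3% to 41%.

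**6. A cut-off suited to the prevalence.** With t = π = 8.7%, sensitivity and specificity are both 72%, 77%, 82% and 88% at c = 0.80, 0.85, 0.90 and 0.95. The same models look very different once the cut-off is stated and suits the event frequency.

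**The case against.** The strongest reply is that the numerical harm comes from a rule the article does not contain. Neither the most probable category nor a 0.5 cut-off is mentioned. The validation paragraph plans several probability thresholds, and a table at those thresholds is an equally natural reading. The rule that turns probabilities into classes may stand in the full protocol or analysis plan. This is right: the figures above are conditional, and the absence of that rule from an article is not itself a fault.

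Other replies also stand in part.

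- A grouped table of observed proportions against predicted risk is feasible. A reader might infer that the analysis cannot be done at all. The documents do not support that: the sentence fails for an individual child and for a confusion matrix, but a calibration-type table could be made, and it would show under-prediction in a subgroup.
- A reader might infer near-zero sensitivity for severe disease in most subgroups. That is not shown. In the enriched sample only the weakest model (c = 0.75) comes close, no actual subgroup was simulated, and values near zero at better c need an assumed low weighted prevalence.
- A full four-by-four table shows where each child lands. A category 1 child placed in category 2 is one level off, and category 2 itself includes later deaths and longer admissions.
- Comparing a default rule with a better-chosen cut-off compares operating points. The gain in sensitivity is paid for in specificity.
- The article does not exclude the c-statistic and calibration from the subgroups. It does not carry them over either.

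What the replies do not remove is the sentence itself. The article chose to name a subgroup measure, and the measure it names is internally inconsistent.

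**Conclusion.** The point holds as a specification error of modest weight that should be corrected. The sentence pairs a confusion matrix with quantities that do not belong in one, and no other measure is tied to the syndrome and aetiology results promised in the abstract.

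If a default class rule were used, the tables would label a minority of category 1 children correctly for c of about 0.75 to 0.90, and differences between syndromes would largely follow event frequency. This rests on 8.7% in category 1 (derived from the article's figures), perfectly calibrated models, and assumed c-statistics and splits of categories 2 to 4. It does not extend to very strong models: at c about 0.95 more than half are labelled correctly, and one split already reaches 52% at about 0.91.

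A reader might also infer that the prediction model or its external validation is compromised. It is not. Derivation, the overall c-statistic, the calibration plots and the threshold examination do not depend on this sentence.

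**What to change.** Replace the sentence with: *In each syndrome and aetiology group, the c-statistic for category 1 and calibration (observed-to-expected ratio and, where events allow, a calibration plot) will be reported with confidence intervals, together with tables of observed outcome category against predicted category 1 risk above or below the same probability thresholds examined in the overall validation.*

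This extends measures the plan already uses and needs no new data. The tables should be read beside the c-statistic and calibration, because sensitivity at a fixed cut-off also moves with event frequency. By the binormal formula, a 0.2 cut-off at c = 0.85 gives 53% at 8.7% prevalence and 65% at 13%.

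The cost is a little more output and wide intervals in small groups. About 117 category 1 events are expected in the whole validation set. An even division over the three syndromes named as examples would leave 117 / 3 = 39 each, and individual aetiologies may have fewer.

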### Patient and public involvement

Prior to finalisation of the study protocol, the concept for the research, study design and sample collection procedures were presented to the Young Persons’ Advisory Group at the Angkor Hospital for Children, Siem Reap, Cambodia. This group, comprising around twenty children aged 10–15 years, provided feedback on the project to ensure alignment with the priorities of the population the research is intended to benefit.

## Discussion

This prospective study will recruit at least 4900 children across seven hospitals in six Asian countries; measure a broad panel of clinical and biochemical biomarkers; and follow participants up over an extended period to determine clinical outcome. It will then follow the latest guidance in clinical prediction model building to derive and geographically externally validate a prognostic clinical prediction model to assist community healthcare providers assess the need for facility-based medical care in children presenting with acute febrile illness in resource-constrained settings across Asia.

Despite increasing interest in clinical prediction research, many studies have limited impact.^38^ This study was designed following the latest guidance^39^: the sample size calculation and recruitment strategy (sampling frame) are based on recent methodological advances,^40 41^ and selection of candidate predictors was informed by expert consensus, feasibility and systematic review of the existing evidence.^31 32 37 42^ Nonetheless, several aspects warrant discussion.

The eligibility criteria for this study are based around fever, yet many children, particularly younger infants, may not mount a fever in response to serious infection. By broadening the eligibility criteria to include hypothermia and history of fever we believe this risk will be partly mitigated. We expect to capture the majority of children with acute infectious illness and hope that ‘abnormal temperature or history of fever’ (rather than, for example, ‘clinician-suspected infection’) will provide a ‘pragmatic point-of-entry’, feasible for lesser-trained community health workers, for use of the clinical prediction tool in the future.

The study will only recruit children aged between 28 days and 5 years, limiting our ability to develop a parsimonious model for all children presenting with suspected infection. In particular, neonates, who carry a disproportionate risk of sepsis, are excluded.^43^ This decision reflects the fact that all febrile neonates require further assessment, and that outside the neonatal period the greatest burden occurs in children under the age of 5 years. Including children of all ages would have required substantially greater resources to ensure adequate power to examine the interaction of predictive performance with age.

Developing a prediction model in settings in which the outcome of interest (in this case, episodes of severe febrile illness) occurs at relatively low frequency poses unique challenges, in particular how best to obtain sufficient precision without requiring an unfeasibly large sample size.^41^ Our stratified recruitment strategy ‘oversamples’ admitted children and provides an ‘enriched’ sample with more ‘outcome events’. This permits evaluation of a greater number of candidate predictors, without increasing the risk of overfitting the prediction model.^40^ Triangulating study data with data from the screening weeks and routine hospital records will provide the necessary information to estimate the denominator (total number of eligible children presenting to the study sites) and weight the regression analysis to develop a prediction model applicable to lower-prevalence community settings.

A further challenge is the choice of outcome (reference standard). We purposively opted not to focus solely on predicting mortality. Although mortality is a ‘hard’ outcome, predicting death may be of limited utility, compared with predicting severe, and in many instances treatable, illness. Furthermore, mortality occurs infrequently and is influenced (mediated) by the level and quality of care, for example, the experience of the healthcare workers and access to interventions such as oxygen, fluids, antibiotics, etc. Estimating a generalisable prediction model (generalisable outside of the studied settings) would necessitate adjustment for the correct set of mediating variables. Adjustment for mediating variables is difficult and can introduce selection bias. To avoid this issue, we have designed ordinal outcome categories, which group children according to the eventual severity of their illness, assessed throughout until day 28.

We recognise that these categories are imperfect, for example, children may remain in hospital for longer than 48 hours for reasons other than illness severity, and outcome misclassification will underestimate the predictive performance of candidate predictors (index tests).^44^ Our protocol-specified analyses are intended to explore this further. We will look to derive a prediction model using data from the subset of children with severe (outcome category 1) and non-severe (outcome category 4) illnesses only (table 3). These binary outcome categories will be less sensitive to misclassification but may not adequately discriminate among more moderately unwell children.^45^ We will, therefore, also develop and validate a pre-specified scale that quantifies illness severity on a continuum.

This study is a first step to developing a tool that a community healthcare provider could use to guide their assessment of whether a febrile child requires referral or admission for facility-based medical care. Operationalising the prediction model developed during this study will require adaptation of the algorithm to electronic and/or paper-based decision-support tools, development of low-cost point-of-care tests for any promising biomarkers for which tests do not already exist, and iterative design in partnership with community health workers and ministries of health. Implementation will need to be supported by development of health worker capacity and contextualised to the insecure contexts in which a tool like this is most urgently needed.

## Ethics and dissemination

This study (protocol V.2.0; 21 January 2020) has received ethical approval from the Oxford Tropical Research Ethics Committee (OxTREC reference: 59–19), the Médecins Sans Frontières Institutional Review Board (MSF IRB reference: 1967) and the relevant institutional and national ethics committees of each participating country. Any necessary protocol amendments will be approved by these same ethics committees prior to implementation. Written, informed consent to participate (and for the storage of clinical data and biological specimens for use in future ethically approved studies with similar aims) is obtained from the parent or legally acceptable representative of all participants.

The study protocol, informed consent materials, SOPs, data management plan and the datasets generated and/or analysed during the current study, are freely available from the MORU and MSF Data Access Committees on reasonable request. Results will be shared with local and national stakeholders, including the local communities at each of the study sites, and disseminated via peer-reviewed open-access journals and scientific meetings.
